### Absorption

In volunteers given 3x 100 mg capsules of unithiol, the drug was detected in blood between 0.5 and 4 hours after ingestion. Maximum concentrations were seen at 4 hours
^
33
^.

In 4 male volunteers, oral bioavailability was 39% (range 19–62%)
^
27
^.

### Metabolism

Unithiol is rapidly and extensively metabolised to disulphide forms, which are not thought to be effective chelators. The predominant urine metabolites of unithiol are as follows: cyclic polymeric unithiol disulphides (97%), unithiol-cysteine mixed disulphide (2.5%) and acyclic unithiol disulphide (0.5%)
^
34
^. In volunteers receiving intravenous unithiol, only 12% of unaltered drug was detected in blood after 15 minutes
^
27
^.

### Distribution

Disulphide metabolites of unithiol are confined to the plasma, suggesting they are plasma protein bound
^
33
^. In a study of three healthy adults who received a single oral dose of unithiol, at 5-hours 62.5% of the total plasma unithiol was protein bound
^
34
^. Most (84%) of the protein bound unithiol was in the form of unithiol-albumin complex, and this is thought to be via disulphide linkage. The remaining non-protein bound drug consisted of unithiol disulphides (36.6%) and unaltered unithiol (0.9%). Amongst five healthy volunteers given intravenous unithiol, the volume of distribution varied from 2.7 to 15.4 L/kg
^
27
^.

### Elimination

Unithiol is subject to renal elimination. In volunteers given intravenous unithiol (3 mg/kg), the elimination half-life was 1.8 hours. Of the total unithiol dose, 10% is found in the urine in an un-altered form, whereas 74% is excreted as disulphide metabolites
^
27
^.

## Justification for this clinical trial

There is an urgent need to develop improved therapeutics for the treatment of snakebite. Every year, over 100,000 people die from snake envenoming, and the burden is particularly high in sub-Saharan Africa and Asia. The World Health Organization has targeted a 50% reduction in morbidity and mortality by 2030, and this trial could be a key step toward achieving this ambitious goal. Unithiol shows promise as a venom inhibitor based on robust pre-clinical measures of efficacy. The advantages of unithiol over antivenom are that it is safe, orally available, demonstrates cross-species specificity and is cheaper to produce. 

Although unithiol has been safely administered to people for many decades, this will be the first study to explore its use as a therapeutic for snakebite. Unlike in heavy metal poisoning, the aim will be to rapidly achieve higher plasma levels, yet it will be possible to stop treatment after only 2 or 3 days. Limited pharmacokinetic data exists for unithiol, and this will be the first trial to investigate the pharmacokinetic effects of multiple doses. This will also be the first trial to evaluate high oral doses, as all previous ‘high dose’ studies have relied on parenteral administration. Oral administration will be important for using this drug in rural tropical settings. As snakebite tends to occur in rural settings, most victims initially present to a rural clinic where an early oral dose of unithiol could be given prior to transfer. Intravenous administration will be important for those cases that present directly to a hospital facility with the capabilities of giving intravenous medications. Considering the dose-responsiveness of unithiol
*in vitro*, as well as the need to rapidly achieve therapeutic levels, intravenous administration may be more efficacious.

## Protocol

### Approvals and trial registration

This trial was registered on the Pan African Clinical Trials Registry on the 3
^rd^ of March 2021 (
PACTR202103718625048).

This manuscript corresponds to the approved version 2 protocol of the TRUE-1 trial, dated 5
^th^ of November 2020. This was approved by the Kenya Medical Research Institute Scientific and Ethics Review Unit on the 13
^th^ of January 2021 and by the Liverpool School of Tropical Medicine Research Ethics Committee on the 18
^th^ of February 2021. Regulatory approval for this protocol was provided by the Kenya Ministry of Health Pharmacy and Poisons Board on the 7
^th^ of August 2021.

This protocol has been prepared in accordance with Standard Protocol Items: Recommendations for Interventional Trials (SPIRIT) guidelines.

## Trial design

This phase 1 open label trial of unithiol in healthy Kenyan adults has a primary outcome of determining safety and tolerability of unithiol. Single ascending doses of oral unithiol will be administered with dose escalation decisions dependent on emerging safety data. Two doses of intravenously administered unithiol will also be administered. Following an interim pharmacokinetic analysis and review of safety data from the single dosing stage, the trial will proceed to a multiple ascending dose stage. Participants will be followed-up for a period of 6-months with full reporting of adverse events and serious adverse events. Safety data will be reviewed by the data safety and monitoring board (DSMB) prior to dose escalations.

## Trial objectives

**Primary objective:** To determine safety and tolerability of unithiol in healthy Kenyan adults.

**Secondary objective:** To define the pharmacokinetic profile of unithiol in healthy Kenyan adults.

**Exploratory objective:** To explore
*ex vivo* efficacy of unithiol at varying doses to inhibit the pathogenic activity of
*Echis ocellatus* and other venoms that rely on SVMPs

## Study site

This single site study will be conducted in Kilifi County, Kenya. Participants will be recruited from Ngerenya, Chasimba and Kilifi township and will reside within the Kilifi Health and Demographic Surveillance System (KHDSS)
^
36
^. Screening, dosing, and follow-up visits will be conducted at a clinical trial facility at Pwani University, Kilifi.

## Recruitment

Members of the KHDSS will be approached using established recruitment strategies such as barazas, health talks, mobilization of community health volunteers and fieldworkers. Information giving sessions will be conducted by appropriately trained study personnel. Individuals who are interested in taking part will have ample time to read the patient information sheet. Contact details will be collected if available in accordance with our data collection policies. Those interested in the trial will be given written patient information in the appropriate language and invited to KEMRI-CGMRC or an appropriate facility for further information giving and informed consent. 

The aim will be to enrol a diverse population from the KHDSS, including rural areas and the Kilifi township. Eligible consenting subjects will be sequentially screened until the required numbers are met. Ideally, equal numbers of male and female subjects will be enrolled (i.e., there will be a cap for each gender) to maintain a representative sample. Female subjects will be asked to demonstrate they are taking appropriate contraception from the screening visit (or the date of access to contraception for participants agreeing to referral to the health facility for this purpose) until 2 months after receiving the study drug (equivalent to two menstrual cycles).

Subjects will be allocated to a dosing cohort using stratified permuted block randomization. Stratification will be according to sex and age.

## Study population

Healthy Kenyan adults will be invited to volunteer for this phase I clinical trial. The study team will aim to enrol people representative of a rural Kenyan population, within the constraints of the inclusion/exclusion criteria. There will be no restrictions based on income, education, and no requirement to speak English language. Ideally, there will be equal numbers of male and female subjects within each cohort.

### Inclusion criteria

Capable of giving informed consentMale or femaleKHDSS resident18–64 years old (inclusive)Body weight 50–120kgIn good health, as determined by the investigator following medical history, drug history, examination, vital signs, electrocardiogram (ECG), and blood testsWilling to be admitted to the in-patient facility for up to 5 days for dosing and intensive blood samplingOn effective contraception as defined by: Use of effective method of contraception for duration of study (women only). We will ask the female volunteers to come with their family planning records to verify. Effective contraception is defined as a contraceptive method with failure rate of less than 1% per year when used consistently and correctly, in accordance with the product label. Examples of these include: combined oral contraceptives; injectable progestogen; implants of etenogestrel or levonorgestrel; intrauterine device or intrauterine system; male partner sterilisation at least 6 months prior to the female subject’s entry into the study, and the relationship is monogamous; male condom combined with a vaginal spermicide (foam, gel, film, cream or suppository); and male condom combined with a female diaphragm, either with or without a vaginal spermicide (foam, gel, film, cream, or suppository).

### Exclusion criteria

Prescribed a concomitant medication other than paracetamol or an appropriate contraceptive, which in the opinion of the Investigator warrants exclusion.Any significant current or history of cardiovascular, respiratory, renal, or hepatic disease.Subjects who have taken any non-prescribed herbal medication or mineral supplement in the preceding 7 days, which in the opinion of the Investigator warrants exclusion.Subject with clinically significant abnormal vital signs at screeningAbnormal laboratory findings deemed significant by the InvestigatorSubjects who are pregnant or lactatingDecline pre-trial screening, including human immunodeficiency virus (HIV) testingHIV positive subjects will be excluded from the trial and, if not already receiving appropriate clinic follow-up, would be referred to a government clinic for ongoing careSubjects with asthma (due to possible risk of exacerbation with allergic type skin reactions to unithiol)Subjects that have donated blood within the past 3 monthsSubjects who in the opinion of the investigator should not participate

### Pre-dose exclusion criteria

Following pre-dose assessments, subjects may be excluded from the dosing cohort for the following reasons. This exclusion may be temporary, and the subject could join a later dosing cohort if the Investigator identifies an abnormality that is likely to resolve within an acceptable period, such as an acute infection.

Clinically significant vital signs or 12 lead ECG findingsClinically significant abnormal laboratory findingsIntercurrent illnessDeviation from study restrictions (unless in the opinion of the Investigator these deviations will not interfere with the study procedures, compromise safety, or affect the study results. Any such deviations will be recorded in the source data and documented in the trial master file (TMF).

## Screening

Subjects will be consented and then screened during a 3-month period prior to being dosed. Participants that are not dosed within 1-month of being screened will be re-screened. It is anticipated that screening will be held once before the single dosing stage and secondly prior to the multiple dosing stage. Additional screening dates may be needed depending on the time taken to dose escalate. The screening visit will be conducted by a clinician at KEMRI-CGMRC or an appropriate facility. The patient information sheet will be given, and the information will be provided verbally and understanding confirmed prior to seeking written consent.

Following provision of written consent, the following information and procedures will be recorded and performed as part of the screening assessments:

Demographics including gender, race/ethnic origin, ageReview of any recent symptoms (including cough, weight loss, fever, night sweats, diarrhoea, dysuria)A comprehensive medical history including a systematic inquiry, a family history, and a history of allergiesPrescribed and non-prescribed medication received in the past 3 monthsConfirmation of contraception use in female subjects of childbearing age
*
Vital signs, including blood pressure, pulse rate, and axillary body temperaturePhysical examinationHeight, weight, and mid upper arm circumference

* Continuous use of an effective method of contraception until 2 months after receiving the final dose of unithiol is required for female participants of childbearing age (unless permanently sterile following hysterectomy). For those with no contraception, they will be referred for contraception at the relevant health facility. For female participants, we will ask them to attend with their family planning records for verification. Effective contraception is defined as a contraceptive method with failure rate of less than 1% per year when used consistently and correctly, in accordance with the product label. Examples of these include combined oral contraceptives, injectable progestogen, implants of etenogestrel or levonorgestrel, intrauterine device or intrauterine system, male condom combined with a vaginal spermicide (foam, gel, film, cream, or suppository), and male condom combined with a female diaphragm, either with or without a vaginal spermicide (foam, gel, film, cream, or suppository).

The following investigations will be undertaken:

Resting 12 lead ECGFor female subjects aged 18 to 64 years: Pregnancy testFull blood countSodium, potassium, urea, and creatinineAlanine aminotransferase (ALT) and bilirubinUrine dip (protein, blood, or glucose)Random blood glucoseViral serology (HBSAg, Hepatitis C virus serology, HIV1 & 2 antigen antibody)Malaria film and malaria rapid test

Once all the above information has been collected, the Investigator will decide if it is appropriate for the subject to be enrolled into the study. Data on all consenting screened subjects will be recorded and the reason for participant exclusions will be documented.

## The investigational medical product (IMP)

The IMP will be Dimaval
^®^ oral capsules and solution for injection sourced from Heyl (the manufacturer).

### Product names

International non-proprietary name: unithiol

Commercial Name: Dimaval
^®^

Synonyms: DMPS, sodium (DL)-2,3-dimercaptopropane-1-sulphonate, sodium 2,3–66 dimercaptopropanesulphonate

IUPAC name: Sodium D,L-2,3-dimercapto-1-propanesulphonic acid

CAS No.: 4076-02-2

Chemical formula: H2C(SH)-HC(SH)-H2CSO-3Na.H2O

Relative molecular mass: 228.28 (monohydrate)

Conversions: 1g = 4.4mmol; 1mmol = 228.3mg; 1g/L = 4.4mmol/L; 1mmol/L = 0.228g/L

### Formulations

The oral form of Dimaval will consist of 100mg capsules. According to the summary of product characteristics, each capsule contains 108.56 mg (RS)-2,3-bis(sulfanyl)propane-1-sulfonic acid, sodium salt 1 H
_2_O corresponding to 100 mg DMPS sodium salt
^
26
^.

The Dimaval solution for injection consists of 5mL volume ampoules containing 250 mg of DMPS-Na. According to the summary of product characteristics, each ampoule contains 271.4 mg (RS)-2,3-Bis(sulfanyl)propane-1-sulfonic acid, sodium salt 1 H
_2_O (DMPS sodium salt 1 H
_2_O) corresponding to 250 mg (RS)-2,3-Bis(sulfanyl)propane-1-sulfonic acid, sodium salt (DMPS-Na)
^
37
^.

### Dose

Participants will be dosed in cohorts of 8. Cohorts for single oral doses are abbreviated as ‘C’, single intravenous dose cohorts as ‘CIV’ and multiple oral dosing cohorts as ‘CM.’ There will be four single ascending oral dosing cohorts (C1-C4), two intravenous dosing cohorts (CIV1 and CIV2) and two multiple dosing cohorts (CM1 and CM2). The anticipated dose escalations are summarised in
Table 2. The dosing regimen in
Table 2 represents the anticipated dose escalations that will be followed should the DSMB have no safety concerns. The highest single oral dose of unithiol that will be administered is 1,500 mg. Any increase above 1,500 mg would require approval from the Sponsor and the ethics and regulatory committees. Following review by the DSMB, dose levels may be repeated, smaller increments in dose escalation may be adopted or dose levels may be lower than the preceding dose level and, therefore, additional cohorts may be included. The DSMB will make these decisions based on adverse event data.

**Table 2. T2:** Summary of dosing regimens.

Single dosing *(and CIV1)*		
Cohort name	Number of subjects	Dose
C1	8	300 mg oral
C2	8	900 mg oral
C3	8	1200 mg oral
C4	8	1500mg oral
CIV1	8	3 mg/kg intravenous single dose
Multiple dosing *(and CIV2)*		
CM1	8	300–1200 mg oral qds for 2 to 3 days
CM2	8	1500 mg oral (or highest tolerated dose from single dosing) qds for 2 to 3 days
CIV2	8	Depends on emerging data (5–10 mg/kg intravenous) single dose

Additional dosing cohorts may be added depending on emerging safety data. Eight cohorts and the above dose escalations represent the maximum dose increases that would occur assuming reassuring safety data.

### Justification for the proposed dose, route of administration, dosage regimen and treatment period

The starting dose for the oral single ascending dose stage will be 300 mg. This is a routine dose recommended for the treatment of heavy metal poisoning
^
38,
39
^. The maximum dose that will be administered during the oral single ascending dose stage will be 1,500 mg. This dose has been selected based on pre-clinical in-vitro assays that have shown that high concentrations of unithiol are required to inhibit the pro-coagulant effects of snake venom
^
21
^. In this experiment, 150 µM of unithiol was required to prevent consumption coagulopathy. Given that previous in-human pharmacokinetic analysis has identified a C
_max_ of 25 µM following administration of 300 mg oral
^
33
^, it has been estimated that a dose of 1,500 mg would be required to achieve a peak plasma concentration sufficient to inhibit coagulopathy. Published reports of dose levels of unithiol equivalent or higher than 1,500 mg oral suggest that this dose is safe
^
24,
31,
32
^.

The dose that will be given to the first intravenous dosing cohort (CIV1) will be 3 mg/kg. This has been selected as it is at the lower range of the routinely recommended dose for acute heavy metal poisoning (3–5 mg/kg)
^
27,
40
^. Previous pharmacokinetic analyses have shown that 3 mg/kg intravenous achieves an initial plasma concentration of 100 µM
^
27
^. At least one further intravenous dosing cohort will be included. The dose administered will be decided by the DSMB based on emerging data from the first stage of the trial. This dose is expected to be 5 mg/kg, although a dose of up to 10 mg/kg may be selected, depending on emerging safety and pharmacodynamic data.

For the multiple dosing cohorts (CM1 and CM2), the study team will select doses that show the optimum profile for treating snakebite, based on safety, tolerability and any available pharmacokinetic and pharmacodynamic data. If the pharmacodynamic data shows a dose response relationship and is deemed to demonstrate sufficient reliability, the investigators will aim to select CM1 based on a minimum dose associated with adequate
*ex vivo* inhibition of SVMPs. The CM2 dose will be selected by the investigators based on the highest dose (between 300 and 1,500mg oral) that is safe and tolerated during single dosing. The preliminary pharmacokinetic data from the single dosing stage will be modelled to identify CM1 and CM2 doses and dose intervals, that will not cause accumulation of the study drug. Ideally, a regimen of no more than four times per day dosing would be preferred (unlike in heavy metal poisoning where 1–2 hourly dosing is used), to optimize adherence to the regimen.

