## Summary of existing pharmacokinetic data for unithiol

In total, four studies on unithiol pharmacokinetics have been conducted by a research group at The University of Arizona. Key finding from these studies are summarised in
Table 1.

**Table 1. T1:** Summary of published human pharmacokinetic data.

Paper	Participants	Dose of unithiol	Main findings
Maiorino 1991 ^ 33 ^	10 male volunteers, aged 24”34 years, weighing 68”98 kg	300mg oral single dose	Absorbed unithiol is rapidly metabolised to disulphide forms. Cmax 11.9 µM, Tmax 3.7 hours, AUC 148 µM hours, half-life 9.1 hours (For total unithiol).
Hurlbut 1994 ^ 27 ^	5 volunteers (4 male, 1 female), aged 24 to 32 years, weighing 49”93 kg	3 mg/kg intravenous single dose	Unithiol is rapidly transformed to disulphide forms (>80% within 15 minutes). Excretion is mostly in urine in disulphide form. Elimination half-life 1.8 hours for parent drug; 20 hours for total unithiol.
Maiorino 1996 ^ 34 ^	4 male volunteers, aged 23 to 27 years, weighing 86”91 kg	300mg oral single dose	Majority of circulating unithiol (>60%) is plasma protein bound. Remaining drug is predominantly in disulphide form (>30%); remainder is unbound parent drug (<1%). Binds to albumin via disulphide complex. Majority of excreted drug is altered and in a disulphide form. Protein bound unithiol theorised to act as a reservoir of the drug and may prolong its activity.
Maiorino 1996 ^ 35 ^	11 factory workers with occupational mercury exposure (7 male and 4 female), mean age 34 years.	300 mg oral single dose	Identified increased mercury excretion and propose using unithiol as a challenge test for identifying mercury poisoning – this approach has since been discredited. Not relevant to present study.

AUC, area under the curve; Cmax, maximum plasma concentration; Tmax, time to maximum concentration.

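### The 1,500 mg oral maximum is justified by a 150 µM target, but the protocol's own figures project 125 µM or 59.5 µM, and its two Cmax values for the same study and dose disagree 2.1-fold

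*Protocol article*

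**What the plan says.** The section justifying the dose, route and regimen builds the oral ceiling in three steps.

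- Target: "In this experiment, 150 µM of unithiol was required to prevent consumption coagulopathy".
- Reference exposure: a Cmax "of 25 µM following administration of 300 mg oral", cited to reference 33.
- Conclusion: "it has been estimated that a dose of 1,500 mg would be required to achieve a peak plasma concentration sufficient to inhibit coagulopathy".

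The Dose section makes 1,500 mg the highest single oral dose; anything above it needs approval from the sponsor and the ethics and regulatory committees.

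Table 1, in the summary of existing pharmacokinetic data, reports the same reference at the same 300 mg oral dose as "Cmax 11.9 µM, Tmax 3.7 hours, AUC 148 µM hours, half-life 9.1 hours (For total unithiol").

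On the form of the circulating drug:

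- The Metabolism section says unithiol is quickly converted to "disulphide forms, which are not thought to be effective chelators".
- The Distribution section reports that, 5 hours after an oral dose in three adults, 62.5% of plasma unithiol was protein bound, 36.6% was unbound disulphide and 0.9% was unaltered.
- Table 1, for another 300 mg study, describes a bound majority and a disulphide share, and says that the "remainder is unbound parent drug (<1"%).

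**The concern.** The justification gives a target, a starting value and a dose, so a reader can check whether the dose reaches the target. On the stated numbers it does not. The starting value is also contradicted by the protocol's own summary table.

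Apart from reports suggesting that the dose is safe, this argument is the only stated basis for where the oral range stops. Ethics and regulatory reviewers were in effect told that the top oral cohort reaches a concentration that blocks venom-induced coagulopathy. If it does not, a clean safety result at 1,500 mg supports safety at that dose but not at an inhibitory exposure. The difference matters because the Conclusions section expects the trial to inform a phase II regimen.

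The missing moiety adds to the problem. An in-vitro concentration of unithiol and a plasma Cmax of total unithiol are not the same quantity if most of the total is in forms that the protocol does not regard as effective chelators.

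**Working it through.** **Inputs**

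| Quantity | Value | Where |
|---|---|---|
| In-vitro target | 150 µM | Dose justification |
| Cmax at 300 mg oral, moiety not stated | 25 µM | Dose justification, reference 33 |
| Cmax at 300 mg oral, total unithiol | 11.9 µM | Table 1, reference 33 |
| Highest single oral dose | 1,500 mg | Dose section |
| Capsule content, hydrate to salt | 108.56 mg to 100 mg | Formulations |

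**1. The plan's own figure.** No scaling model is stated, so dose-proportional Cmax is assumed:

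Cmax(1,500) = Cmax(300) × 1,500/300 = Cmax(300) × 5

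- From 25 µM: 5 × 25 = 125 µM. Shortfall 1 − 125/150 = 17%.
- From 11.9 µM: 5 × 11.9 = 59.5 µM. Shortfall 1 − 59.5/150 = 60%.

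The implied 150 µM is not reproduced from either value.

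**2. The same check in reverse.** The rise in Cmax needed to reach 150 µM is 150/25 = 6.0-fold or 150/11.9 = 12.6-fold. The dose rises 5-fold. Cmax would have to increase more than in proportion to dose, and the protocol gives no reason to expect that.

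**3. The contradiction.** 25/11.9 = 2.1. One reference at one dose has two peak values. The Interim visits section cites the same reference for a half-life of 4 hours, against 9.1 hours in Table 1. The Absorption section describes that study's measurements as blood concentrations, whereas the abbreviation list defines Cmax as a plasma value. These differences would fit a mix of moieties or matrices from one source, but the protocol does not say so.

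**4. Does a salt correction close the gap?** The mass ratio is 108.56/100 = 1.0856.

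- 125 × 1.0856 = 135.7 µM; 125/1.0856 = 115.1 µM.
- 59.5 × 1.0856 = 64.6 µM; 59.5/1.0856 = 54.8 µM.

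All remain below 150 µM.

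**5. Does the intravenous figure close it?** The protocol gives 100 µM initially after 3 mg/kg intravenous, and oral bioavailability of 39% (range 19–62%). With instantaneous absorption and an assumed weight of 70 kg:

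- 1,500 mg: (1,500/70) × 0.39/3 × 100 = 279 µM. Over 50–120 kg and 19–62% bioavailability the range is 79 to 620 µM.
- 300 mg: (300/70) × 0.39/3 × 100 = 56 µM, against a reported 25 or 11.9 µM.

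At these central values the method overstates the oral peak 2.2-fold (56/25) to 4.7-fold (56/11.9). It ignores slow absorption, and the protocol does not use it. It does not support the stated estimate.

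**The case against.** The strongest reply is that the sentence speaks of an estimate, that the gap on the figure it actually uses is only 17%, and that any step from an in-vitro assay to plasma is rough. The trial will measure Cmax at each dose level and test venom inhibition ex vivo, so data will replace the projection. The Conclusions section itself says more information on the oral dose is needed before phase II. All of that is fair, and it limits the consequence. It does not make 125 equal 150, and it does not explain two Cmax values for one study and dose. Reading the sentence as naming only a minimum dose does not help either, because the inputs still do not lead to 1,500 mg.

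The 60% shortfall holds only if the Table 1 value is the comparable one, which cannot be settled without the cited study.

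A reader might go further in three ways that the documents do not support.

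- **That almost all of the projected peak is inactive, leaving about 0.5 to 1.1 µM of parent drug** (0.009 × 59.5 and 0.009 × 125). The 0.9% share comes from three adults at 5 hours in a different study, not at the 3.7-hour peak. The moiety behind 25 µM is not stated. The protocol says only that disulphides are not thought to be effective, and Table 1 raises the idea that bound drug acts as a reservoir that may prolong activity.
- **That the CM2 cohort depends on the 150 µM claim.** CM2 is the highest dose found safe and tolerated in single dosing. The claim reaches it only through the 1,500 mg cap.
- **That both parent and total drug can be tabulated against the target.** The article does not say that the assay measures both.

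**Conclusion.** The stated basis for the oral maximum is wrong as written. Assuming dose-proportional Cmax, 1,500 mg projects to 125 µM from the figure in the dose justification (17% short of 150 µM) or 59.5 µM from Table 1 (60% short). The 2.1-fold conflict between the two Cmax values needs no assumption; it stands on the page. The comparison with the in-vitro concentration is also undefined, because the moiety is not named while other sections describe most circulating drug as bound or disulphide.

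The linearity assumption is the reviewer's, since the protocol states no pharmacokinetic model. The form behind 25 µM is unknown. The finding therefore shows that the protocol's figures do not support the claim of an inhibitory peak; it does not show that such a peak cannot occur. It concerns the oral rationale only. Escalation is decided on adverse events and the primary objective is safety and tolerability, so neither the primary analysis nor the escalation rules change. What changes is the exposure that the trial can claim to have tested.

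**What to change.** 1. Reconcile the Cmax values in Table 1 and the dose justification, giving matrix (blood or plasma) and moiety (parent or total) for each. Check the two half-lives cited to the same reference at the same time.
2. Restate the rationale with the corrected projection and an explicit linearity assumption. Say which form of the drug the 150 µM target refers to. Unless the reconciled figure supports it, remove the statement that 1,500 mg is estimated to give an inhibitory peak.
3. In the report, set the observed Cmax of each cohort, already a planned output, beside 150 µM for whichever moiety the assay measures, so that tolerability at 1,500 mg is not presented as tolerability at an inhibitory exposure.

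The cost is a change of wording and one comparison drawn from planned measurements. The published rationale may become less favourable. Which dose is appropriate is for the sponsor, investigators and DSMB; none is proposed here.
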